#### Sample size

The calculation of the sample size considered followed assumptions:

-A total of 95% confidence level;-The drop-out rate of 10%;-Expected difference between the two treatments for 3-month and 6-month VT burden in terms of overall response rates: 20% higher in arm including VT-ART compared to the control group;-Power of 80%.

To improve clinically adequate balancing, we will enroll two matching paired patients in the group not undergoing VT-ART for each patient who undergoes VT-ART in a 2:1 ratio, favoring a larger proportion of patients not undergoing the innovative procedure (i.e., VT-ART).

Under these hypotheses, to detect a 20% improvement in the VT burden control rate in the VT-ART group vs. the control group, we calculated the sample size (in a 2:1 ratio) upon enrolling 149 patients: 100 in the non-exposed control group and 49 in the VT-ART group. Progressively, on a multicentric basis supervised by the promoting center in the VT-ART consortium, for each VT-ART patient enrollment, a matched pair patient profile according to the predefined features will be shared with the consortium to enroll two similar patients who have not undergone VT-ART. For enrollment into the control group, recruitment of clinical cases from retrospective case series within the multicentric consortium will also be allowed, with the only condition to be not earlier than 5 years from the enrollment of the matched pair patient in the VT-ART group (to avoid the possible influence of a too early approach for standard procedures).

All statistical analyses will be performed using SPSS^®^ version 25.0 software (©Copyright IBM Corporation 1994, 2017).

Due to the potential difficulty of enrolling the patients through the complete match of all matching factors, a protocol rule will be applied through patient’s collection.

Once the planned number of the innovative procedure will be collected, the trial will put a 6-month observation time. If after that, 60% of the planned conventional arm patients will be collected (by all matching factors and in a 2:1 ratio), a further 3 months will be provided to reach the planned accrual. If that would have not been the case, then the patient’s enrollment will be allowed by mandatory matching factors only (only beyond that point). The detail of “mandatory matching factors” is reported in Table 2. The final analysis will be performed by the whole group and subgroup analyses, discriminating patients collected through “all matching factors” and by “mandatory-only.”

The final analysis will not be performed at all if less than a 1:1 ratio (conventional: Innovative group) of patient’s enrollment will be collected, and the study will be closed.

The final analysis will be performed specifying that the planned accrual is not met if at least a 1:1 ratio (conventional: Innovative group) enrollment will be accomplished; results will be explored and cautiously evaluated.

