## Outcome measures

The primary outcome is investigating the difference in overall cardiovascular survival among the group undergoing VT-ART and the one not exposed to the innovative procedure.

The primary efficacy endpoint is a statistically significant difference in overall cardiovascular survival between the group undergoing VT-ART and the one not exposed to the innovative procedure; this will be defined in months and calculated from the time of the last procedure (represented by the last RFA for the control group and VT-ART for the innovative one, respectively).

The secondary outcome is evaluating the difference in ventricular event-free (referred to VT/VF, appropriate shock or ATP as recorded by the ICD) survival after the last procedure between the two groups (i.e., the single or last RFA in the control group and VT-ART in the innovative group). The respective endpoint is a statistically significant difference in ventricular event-free survival (in months) after the last procedure between the two groups.

An additional secondary aim is to evaluate the reduction in the number of VT episodes compared to the pre-treatment period between the two dynamic cohorts that will be investigated.

Ventricular tachycardia recurrence will be defined as evidence of monomorphic VT at ICD interrogation (either self-limiting or terminated by appropriate shock therapy or ATP). The number of VT episodes, defined as VT burden, in the 3 months before and after the procedure will then be compared.

The respective secondary endpoint will be evaluated facing 3 months before the last procedure (i.e., either RFA or VT-ART) and 3 months after.

We did set a blanking period after VT-ART before evaluate the effect on VT burden; in a recent study by Kautzner et al., the authors supported the pre-clinical theorem of myocardial apoptosis (up to 3 months post-stereotactic ablation) followed by a creation of fibrotic lesion (6–9 months post-stereotactic ablation) in the irradiated region (5). Consequently, we propose a 3-month-blanking period after the procedure.

Since a blanking period of 3 months after the procedure will be applied, the secondary endpoint will evaluate the number of VT episodes interval accounted for the last 3 months before the procedure and of the 3–6 months after it.

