## Discussion and final considerations

Sustained monomorphic VT is a potentially life-threatening condition that often affects patients with structural heart diseases. VT recurrence poses a severe threat to health and quality of life. Long-term management of recurring VT relies mainly on ICDs, pharmacological control (i.e., class III antiarrhythmic), and RFA of the pathological arrhythmogenic substrate.

New long-term solutions are currently being sought for patients in whom VT is refractory to conventional treatment strategies or in whom it cannot be performed. In patients with structural heart disease, the rate of VT recurrence after RFA has been reported to be between 25 and 50% (8). Intrinsic technical aspects of the procedure (e.g., difficult anatomical location of the arrhythmic substrate) as well as patient-related factors (e.g., patient frailty) may limit RFA feasibility in a portion of the population. Patients with structural heart disease are often fragile and have a varying number of comorbidities. Therefore, procedure invasiveness could be a limiting factor in the choice of the best treatment strategy (9).

Cuculich et al. first investigated the efficacy and safety of stereotactic radiation for the ablation of VT in a five-patient case series, which was later followed by the publication of a phase I/II prospective study by the same authors, including 19 patients (1, 2). Both studies reported a statistically significant reduction (99.9 and 94%, respectively) in VT episodes after a blanking period of 4 weeks. Subacute and chronic treatment-related side effects ranged from asymptomatic pericardial effusion to radiation-induced pericarditis and pneumonitis and were successfully treated with corticosteroids. Since then, a growing number of scientific articles have been published on this matter.

Overall, VT-ART has been proven to be an effective and adequately safe intervention in other studies (10, 11). Its non-invasive nature makes it a safe alternative for patients who are not suitable for percutaneous RFA (9). Nevertheless, despite the promising results detected by sporadic reports, limited case series, and systematic reviews (12), we still do not know if and at what level VT-ART (and STAR in general) could significantly and effectively improve the clinical scenario of such complex malignancies.

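### The 149 patients and 80% power are calculated for a secondary VT-burden rate, not for cardiovascular survival, and even there the 80% depends on an unstated control rate

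*Protocol article*

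**What the plan says.** Under Outcome measures the protocol article sets the primary endpoint: "The primary efficacy endpoint is a statistically significant difference in overall cardiovascular survival between the group undergoing VT-ART and the one not exposed" to VT-ART. It is measured in months from the last procedure. VT burden stands lower in the hierarchy: "An additional secondary aim is to evaluate the reduction in the number of VT episodes compared to the pre-treatment period". There it is defined as a number of episodes, comparing the 3 months before the procedure with months 3 to 6 after it, following a 3-month blanking period.

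Under Sample size the inputs are a 95% confidence level, 80% power, 10% drop-out and a 2:1 ratio of controls to VT-ART. The effect is a VT-burden response rate "20% higher in arm including VT-ART compared to the control group". The result is 149 patients, 100 controls and 49 VT-ART, sized "to detect a 20% improvement in the VT burden control rate in the VT-ART group vs. the control group".

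The section gives no control rate and no sidedness, and does not say whether 20% is absolute or relative. The only related figure is in Discussion and final considerations: "the rate of VT recurrence after RFA has been reported to be between 25 and 50" percent, in patients with structural heart disease. It is not linked to the calculation.

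**The concern.** The only power statement in the document belongs to a different outcome from the one on which efficacy is judged. The two also differ in kind: the primary is a time to event, the sizing variable is a proportion, and VT burden as an endpoint is a count. The abstract names cardiovascular survival as primary and later gives 149 without saying what that number is powered for.

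Two things are at stake. First, a non-significant survival result could be read as evidence of no difference, although the trial was never sized to detect one. Second, the power of a two-proportion comparison with a fixed difference depends strongly on the control rate. Without that rate, nobody can confirm that 149 patients give 80% power even for VT burden.

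**Working it through.** **Inputs from the document.** 100 controls and 49 VT-ART; drop-out 10%; 80% power; 95% confidence level.

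**Assumptions, because the document is silent.** Two-sided 5%; 20% means 20 percentage points; groups treated as independent (no within-set correlation from the matching is given); pooled null variance.

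**Evaluable patients.** 100 × 0.9 = 90 controls; 49 × 0.9 = 44.1, taken as 44 VT-ART; total 134.

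**Step 1: can 149 be reproduced?** With pT and pC the rates and p̄ = (pT + 2pC)/3, the VT-ART group needs

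n = [1.96·√(1.5·p̄(1−p̄)) + 0.842·√(pT(1−pT) + pC(1−pC)/2)]² / (pT−pC)².

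- 72 vs 92%: p̄ = 0.787; n = (0.983 + 0.351)² / 0.04 = 44.5; total 3n = 133.6; divided by 0.9, 148.5, so 149.
- 10 vs 30%: n = 43.5; total 130.6; divided by 0.9, 145.
- 10.5 vs 30.5%: n = 44.5; total 133.4; divided by 0.9, 148.2, so 149.
- 50 vs 70%: n = 70.3; total 210.8; divided by 0.9, 234.

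So 149 fits the stated inputs near two control rates, about 10% and about 72%. The document does not say which, if either, was used.

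**Step 2: power of 90 + 44 at other control rates.** Power = Φ{(0.20 − 1.96·s0)/s1}, where s0 = √[p̄(1−p̄)(1/44 + 1/90)], s1 = √[pT(1−pT)/44 + pC(1−pC)/90] and p̄ = (44pT + 90pC)/134.

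At 50 vs 70%: p̄ = 0.566, s0 = 0.0912, s1 = 0.0869; (0.20 − 0.1787)/0.0869 = 0.245; power 60%.

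| Control vs VT-ART | Power, 134 evaluable | Power, all 149 evaluable |
|---|---|---|
| 50 vs 70% | 60% | 64% |
| 60 vs 80% | 65% | 70% |
| 70 vs 90% | 76% | 81% |
| 75 vs 95% | 86% | 90% |

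With 134, power is below 80% for control rates from about 10.5% to 72%, with a minimum of 59% near 43%. With all 149 the range is about 13% to 69%. Exact binomial power is close (61%, 66%, 78% and 89% for the four rows with 134).

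**Step 3: sensitivity to the assumptions.** One-sided 5% moves the limits for 134 to about 18% and 64%. If 20% is relative, power at a 70% control rate (70 vs 84%) is 41% with 134 and 45% with 149.

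**Step 4: set against the protocol's own recurrence figure.** Recurrence of 25–50% means, as a rough proxy, 50–75% controlled. Two-sided power falls short of 80% from 50% to about 72%, that is 22 of the 25 points.

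**Step 5: illustration for the primary endpoint.** The document gives no mortality. Assume 36-month control cardiovascular mortality m of 30–50%, with VT-ART mortality 1 − (1−m)^HR and 2:1 allocation (factor 2/9).

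- Events needed at HR 0.5: (1.96 + 0.842)² / [(2/9)(ln 0.5)²] = 7.85/0.1068, about 74.
- Events expected at HR 0.5: m = 30%, 27 + 7.2 = 34; m = 50%, 45 + 12.9 = 58.
- Power = Φ{√(events × 2/9)·|ln HR| − 1.96}: at HR 0.5, 48% to 70%; at HR 0.6, 30% to 46%.
- HR detectable with 80% power: about 0.35 (m = 30%) to 0.45 (m = 50%).

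**The case against.** The strongest reply is that no arithmetic error has been shown. At about 72 vs 92% the stated inputs return 149, and that control rate lies inside the 50–75% proxy, so it is not an extreme value. About 10 vs 30% is also conceivable in a refractory population. This stands. A reader might infer from the power table that the sample size was miscalculated, or that it works only at implausible rates. The document supports neither.

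The thresholds also rest on choices the article does not state: sidedness, variance formula and independence despite 1:2 matching. This stands too, so they must be read as conditional. One-sided testing narrows the failing range but does not remove it.

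The recurrence figure is a weak proxy. A patient can have a recurrence and still have a reduced burden, while the enrolled patients are selected for refractory VT. The true control rate could lie on either side of 50–75%.

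The survival figures follow from an assumed mortality. That is correct; they illustrate and do not establish the trial's power.

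A reader might also take the article to claim 80% power for cardiovascular survival. It does not: the Sample size section names VT burden as its target twice. The defect is the missing link to the primary endpoint, not a false statement about it. VT burden is moreover a listed secondary endpoint; what differs is that a count is used there as a rate.

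None of this answers the main point. The article sets out its sample-size assumptions, and they concern an endpoint other than the primary.

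**Conclusion.** The point holds in two parts of different strength.

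First, the stated 80% power does not apply to cardiovascular survival. This follows from comparing the two sections and needs no assumption.

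Second, the 80% for VT burden is conditional and cannot be checked. With 20 percentage points, two-sided 5%, independent groups and 90 + 44 evaluable patients, it requires a control rate of at most about 10% or at least about 72%. In between, power falls as low as 59%. Most of the range suggested by the protocol's rough recurrence proxy falls short, but its upper end does not. The conclusion is that 149 is unverifiable and sensitive to the missing rate, not that it is wrong.

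How far the trial falls short for the primary endpoint is unknown without a mortality assumption. Under 30–50% control cardiovascular mortality at 36 months, only a hazard ratio of about 0.35–0.45 or stronger would be detected with 80% power.

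**What to change.** Keep 149 patients and change the wording of the Sample size section:

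- Say that the calculation concerns VT-burden response in the window after blanking, and does not cover the primary endpoint.
- State the assumed control rate, the sidedness of the test, and whether 20% is absolute or relative. Give the power at that rate, and keep 80% only if the rate supports it.
- For cardiovascular survival, state the detectable hazard ratio under declared mortality assumptions. The 0.35–0.45 above is an illustration; the sponsor should use its own mortality figures.
- Report cardiovascular survival as an estimate with a confidence interval, and say that a non-significant result will not be read as no difference.

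The cost is a revised paragraph and probably a less favourable power statement. No extra patients are needed.

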**Discussion:**

The aim of this multicenter observational study is to evaluate the efficacy and safety of VT-ART, comparing the clinical outcome of patients undergone to VT-ART to patients not having received such a procedure. The two groups will not be collected by direct, prospective accrual to avoid randomization among the innovative and traditional arm: A retrospective selection through matched pair analysis will collect patients presenting features similar to the ones undergone VT-ART within the consortium (in each center independently). Our trial will enroll patients with optimized medical therapy in whom endocardial and/or epicardial radiofrequency ablation (RFA), the gold standard for VT ablation, is either unfeasible or fails to control VT recurrence. Our primary outcome is investigating the difference in overall cardiovascular survival among the group undergoing VT-ART and the one not exposed to the innovative procedure. The secondary outcome is evaluating the difference in ventricular event-free survival after the last procedure (i.e., last RFA vs. VT-ART) between the two groups. An additional secondary aim is to evaluate the reduction in the number of VT episodes comparing the 3 months before the procedure to the ones recorded at 6 months (from the 4th to 6th month) following VT-ART and RFA, respectively. Other secondary objectives include identifying the benefits of VT-ART on cardiac function, as evaluated through an electrocardiogram, echocardiographic, biochemical variables, and on patient quality of life. We calculated the sample size (in a 2:1 ratio) upon enrolling 149 patients: 100 in the non-exposed control group and 49 in the VT-ART group. Progressively, on a multicentric basis supervised by the promoting center in the VT-ART consortium, for each VT-ART patient enrollment, a matched pair patient profile according to the predefined features will be shared with the consortium to enroll a patient that has not undergone VT-ART.

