## Protocol overview

With current knowledge, it is difficult to set a randomized trial between a population undergoing VT-ART (e.g., in the compassionate setting often applied for patients proposed for such an innovative procedure) and a population not undergone to that. Randomizing a patient’s accrual to VT-ART instead of the conventional option implies that some patients would skip a conventional procedure in favor of a procedure still considerate at least still non-standard, although promising. Multiple, reliable phase I and phase II trials are not available, although case series and at least one phase I/II trial have investigated VT-ART efficacy (1).

Finally, it would be difficult to define two balanced treatment arms that are suitable for a clinical randomized comparison, since patients undergoing VT-ART would have either already received RFA or are unable to receive it, and they have already undergone other standard treatments. On the other hand, setting a single-arm trial would test less efficiently the clinical of VT-ART and could imply the adoption of VT-ART only for worse clinical case presentations.

This multicenter observational study will evaluate the efficacy and safety of VT-ART. Our trial will enroll patients with optimized medical therapy, in whom endocardial and/or epicardial RFA is either unfeasible or fails to control VT recurrence. The trial is set as observational since it indirectly comparing VT-ART with a conventional procedure (i.e., RFA).

Each patient recruited for VT-ART will be profiled according to a predefined list of characteristics that will be circulated within the centers participating to the consortium to collect other patients with a similar profile, not having undergone VT-ART, for final analysis.

The peculiar setting of our trial will avoid precluding VT-ART to patients possibly taking advantage of such a therapeutic option; moreover, it will compare VT-ART with retrospective series not having receive VT-ART anyway. Furthermore, this approach will retrieve otherwise sporadic data about single or limiter case series of each center joining the consortium. This trial is not strictly investigational but can add notable scientific information to the current scenario.

The multicenter setting of this study will allow for faster recruitment of the sample size.

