Multicenter recruitment will allow for a more precise assessment of the effects of VT-ART, with the aim of demonstrating that implementing such a procedure is both feasible and safe among centers. Moreover, it will increase the chances to recruit patients with profiles matching the ones in the arm undergone VT-ART.

A standardized data collection has been defined for data regarding both VT-ART and RFA.

The trial will thus both collect prospective and retrospective data about VT-ART (following the predefined standardized data collection). Prospective data collection will be applied within the consortium for the patients referred to VT-ART after the beginning of the trial; retrospective data collection will be allowed for the VT-ART procedure delivered before the formal start of the trial if the data required by the predefined standardized data collection are available for defining the primary and secondary endpoint (see following sections). Similarly, prospective and retrospective data collection will be allowed for data about conventional treatment (i.e., RFA).

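### Controls may date from up to 5 years before their VT-ART match, and neither the matching factors nor the fixed subgroup split accounts for procedure date or collection mode, so differences in era and ascertainment can pass as a VT-ART effect.

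*Protocol article*

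**What the plan says.** **Age of controls.** The Sample size section lets control patients also be drawn from past case series of the participating centres, "with the only condition to be not earlier than 5 years from the enrollment of the matched pair patient in the VT-ART group". The reason given is "to avoid the possible influence of a too early approach for standard procedures". The limit is counted from the VT-ART patient's enrolment.

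**Source of controls.** The abstract says "A retrospective selection through matched pair analysis will collect patients presenting features similar to the ones undergone VT-ART within the consortium". The Protocol overview says "it will compare VT-ART with retrospective series not having receive VT-ART anyway". The same overview then admits both modes for conventional treatment: "Similarly, prospective and retrospective data collection will be allowed for data about conventional treatment (i.e., RFA").

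**Source of VT-ART patients.** The Protocol overview states "Prospective data collection will be applied within the consortium for the patients referred to VT-ART after the beginning of the trial". It adds that "retrospective data collection will be allowed for the VT-ART procedure delivered before the formal start of the trial" where the required data exist. No look-back limit is given for these cases.

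**Follow-up.** Prospective VT-ART patients have scheduled ICD interrogations. Prospective RFA patients follow the same schedule only where possible. Retrospective patients of either group have data extracted from records at the same time points.

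**Matching and analysis.** Table 2 lists 18 factors, 8 of them mandatory. The statistical section repeats most of them and adds intervals in days between earlier procedures and VT-ART. The between-group tests named are chi-square, t-test or non-parametric tests. The only subgroup split fixed for the final analysis is between patients matched on all factors and those matched on mandatory factors only.

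**The concern.** The comparison is not randomised, so its credibility rests on how controls are chosen. The protocol recognises that the era of standard treatment may influence results, but its only response is a 5-year cap. Within that cap nothing favours a control treated last year over one treated almost five years ago, and nothing balances the collection mode.

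Two things could then differ between the groups besides VT-ART. One is calendar time: if survival or background care improves over the years, older controls do worse for that reason alone. The other is ascertainment: events from scheduled device checks and events from old records need not be found equally completely. Neither would shrink with more patients. At stake are the primary comparison of cardiovascular survival and the secondary comparisons of ICD-recorded events.

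**Working it through.** **1. Is date or mode controlled anywhere in what the document fixes?**

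| Place | Calendar date of procedure | Prospective/retrospective mode |
|---|---|---|
| Table 2 (18 factors, 8 mandatory) | no | no |
| Matching list in the statistical section | no; its time items are intervals between procedures | no |
| Subgroup split (Sample size) | no | no |
| 5-year rule (Sample size) | upper limit on age only | no |

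**2. What does the 5-year rule measure?** It runs from the VT-ART patient's enrolment, whereas survival is counted from the last procedure (Outcome measures). For a retrospectively collected VT-ART patient, enrolment may come well after the procedure. If that gap is L years, the same rule allows a control procedure up to 5 − L years before the VT-ART procedure, and also allows one after it. The cap therefore does not bound the procedure-to-procedure gap in a uniform way.

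**3. Illustration for the primary endpoint.** The plan states no figure for an era effect, so there is nothing to reproduce, and it gives no yearly change in hazard. Assume a fall of d = 2%, 3% or 5% per year and no true VT-ART effect. A control treated *lag* years earlier then gives

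spurious HR = (1 − d)^lag.

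| Mean lag | d = 2% | d = 3% | d = 5% |
|---|---|---|---|
| 1.25 years | 0.975 | 0.963 | 0.938 |
| 2.5 years | 0.951 | 0.927 | 0.880 |
| 5 years (limit) | 0.904 | 0.859 | 0.774 |

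A lag of 2.5 years assumes that all controls are retrospective and spread evenly over the window (5/2). A lag of 1.25 years assumes that half of them are contemporaneous (0.5 × 2.5 + 0.5 × 0). The last row requires every control to sit at the limit.

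**4. Illustration for the VT-burden response used for sizing.** Inputs from the protocol are 49 VT-ART patients, 100 controls, a 5% significance level (taken as two-sided) and a planned difference of 20%, read as 20 points. Assume no true effect, a VT-ART response rate p1 of 50% to 75%, and a net era or ascertainment shift Δ against controls, so that p2 = p1 − Δ. For the pooled two-proportion test,

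P(significant in favour of VT-ART) = Φ[(Δ − 1.96·se0)/se1].

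Example with p1 = 0.60 and p2 = 0.50:
- pooled rate = (49 × 0.60 + 100 × 0.50)/149 = 0.533
- se0 = √[0.533 × 0.467 × (1/49 + 1/100)] = 0.0870
- se1 = √(0.24/49 + 0.25/100) = 0.0860
- Φ[(0.10 − 1.96 × 0.0870)/0.0860] = Φ(−0.82) = 0.206

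Over p1 = 50%, 60% and 75%:

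| Assumed shift Δ | Chance of a false result favouring VT-ART |
|---|---|
| 0 | 2.5% (nominal) |
| 5 points | 8–9% |
| 10 points | 21–23% |
| 15 points | 40–43% |

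A 10-point shift is half the planned effect. The documents give no evidence on its actual size.

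**The case against.** **The direction is not fixed by design.** A reader might infer that controls are always earlier than their match. The documents do not support this. After each VT-ART enrolment the profile is circulated so that two similar patients can be enrolled. Prospective RFA data are allowed, and control accrual continues for 6 months, possibly 3 more, after the planned VT-ART number is reached. VT-ART cases may themselves be retrospective without a stated look-back limit. Controls can therefore be contemporaneous or later. This objection stands, and it limits the claim about direction.

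**The share of retrospective controls is unknown.** It is tempting to say that most controls are retrospective. The abstract and one sentence of the Protocol overview point that way, but the Sample size section presents such cases as an additional source, and no proportion is given. It is equally tempting to say that every matched set is affected. A set in which all members share the same collection mode is free of the mode difference.

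**Ascertainment may matter less than feared.** Death depends little on scheduled visits, arrhythmic events are device-recorded, an ICD is an inclusion criterion, and analysis is limited to patients with data at the time points. This weakens the ascertainment argument for the primary endpoint. It does not equalise scheduled interrogation with record extraction for the arrhythmic endpoints, and it does nothing about era.

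**Covariates belong to the SAP.** This is partly right: silence on a survival model is not a fault here. But the 5-year rule, the matching list and the subgroup split are fixed in this document and act during enrolment. A later SAP could adjust for date, but it could not replace distant controls already chosen.

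**Conclusion.** The point holds in a limited form. The protocol names era as a possible influence and caps it at 5 years, but neither the matching nor the fixed subgroup split accounts for procedure date or collection mode. Era and ascertainment differences can therefore pass as a VT-ART effect.

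Their amount cannot be known from the documents. Favouring VT-ART is the likely direction, because the comparator is described as retrospective while new VT-ART patients are followed prospectively. It is not certain.

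The hazard ratios of 0.95–0.88 (mean lag 2.5 years) and 0.975–0.94 (1.25 years) show scale only. They rest on an assumed yearly fall of 2% to 5% and on assumed date distributions. The 0.77 at the 5-year limit is an extreme and should not be read as an expected bias.

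This should be changed before more controls are selected. It does not by itself invalidate the study.

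**What to change.** 1. Where more than two controls satisfy the matching factors, take those whose index-procedure dates are closest to the VT-ART procedure date.
2. Count the 5-year limit from procedure to procedure.
3. Record procedure date and collection mode for every patient, and report their distribution by group.
4. Adjust the between-group comparison for procedure year.
5. Add a sensitivity analysis limited to matched sets whose members share the same collection mode.

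**Cost.** The selection rule adds one step to the control search, but it helps only where surplus eligible controls exist, and the protocol itself expects difficulty in finding complete matches. Adjustment for year widens intervals, possibly substantially if year and group are strongly correlated. With 49 planned VT-ART patients, the same-mode subset may be small. Collection mode is better handled by that sensitivity analysis than as a model covariate, because it may be nearly collinear with group. The case report form is not shown, so whether date and mode are already captured has to be confirmed.
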